#### Follow up measurements

Consistent with a previous comparable RCT [15], participants will be invited (via e-mail) to fill-out questionnaires at 1, 2, 3 and 6 months post-ESM (online via the RoQua system). The participants will be able to fill out these forms at home. In case of non-response, participants will receive an e-mail and text message after 3 days to motivate them to fill out the questionnaires. A complete overview of the (timing of the) questionnaires is presented in Additional file 2: Table S2 in the Study Parameters section.

#### Interview

To get a better view on whether ZELF-i has added value to standard care, two psychologists will individually interview a subset of participants in the two intervention groups. The interviews will last for one hour and take place at the mental health care organization. Not all participants will be contacted for an interview; participants will be selected at random until data saturation is complete. Selected participants will be contacted by one of two psychologists by telephone within 8 weeks after the debriefing to answer questions and invite them to take part in the interview. Participation in the interview is optional, and independent of continued participation in the follow-up measurements. At the interview appointment, participants will be asked to sign a consent form specific to the interview. The interview will be recorded with audio equipment and processed into a transcript. The anonymized transcripts will be coded independently by two psychologist researchers, followed by a consensus discussion under supervision of a qualitative research expert. After data coding, the audio recordings will be destroyed.

### Data management

Data will be handled in a strictly confidential manner, complying with the Dutch Personal Data Protection Act (*Wet Bescherming Persoonsgegevens*). Each participant will be assigned a unique identification number in order to protect privacy. During data collection, team members will have access to the contact details of the participants in order to contact them. After data collection, only the principal investigator ([name]) of this study will have access to the coding of the subjects. Other investigators only have access to the coded files that do not contain information that can be traced to a specific individual. ESM and questionnaire data will be stored in Medoq, a research environment within RoQua, which cannot be accessed by practitioners. Participants choose themselves whether they want to share their feedback reports based on the ESM measurements with their practitioners. Any non-digitalized questionnaire data will be kept in locked cabinets in the investigator’s office.

As this intervention study does not include medical procedures we do not expect any serious adverse events to occur. Any undesirable experience reported spontaneously by the participants or observed by the investigator or her staff during the study, whether or not considered related to the experimental treatment, will be recorded as an adverse event. For each participating centre, the principle investigator will notify the coordinating investigator of any adverse and serious adverse events. A data monitoring committee has not been installed as the added risk in comparison to care as usual is negligible.

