**Methods:**

The ZELF-i study is a pragmatic multi-site randomized controlled trial (RCT). We aim to recruit 150 individuals with depressive symptoms aged between 18 and 65 years, who have an intake for outpatient basic or specialized treatment at a mental health care organization in the North of the Netherlands. After the intake, participants will be randomly allocated to one of three study arms: two experimental groups engaging in 28 days of systematic self-monitoring (5 times per day) and receiving weekly personalized feedback on positive affect and activities (“Do”-module) or on negative affect and thinking patterns (“Think”-module), and a control group receiving no additional intervention. Self-report inventories of depressive symptoms, psychosocial functioning and feelings of empowerment will be administered before and after the intervention period, and at follow-up measurements at 1, 2, 3 and 6 months. The patient-experienced utility of the intervention will be investigated by a combination of quantitative and qualitative research methods.

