#### Introduction session and baseline measurement

The introduction session will take place at the mental health care organization. At the start of the introduction session, participants will have another opportunity to ask questions about the study procedures. If everything is clear, they will be asked to provide written informed consent. After the informed consent procedure, participants will be randomly allocated to the control group or one of two ESM intervention groups. Then, detailed instructions and practice runs for the ESM modules follow, depending on the allocated treatment condition. Finally, all participants will fill out questionnaires assessing characteristics at baseline, depressive symptomatology, functioning, empowerment, and questionnaires necessary for cost-effectiveness analyses (see Study Parameters section).

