**Fig. 2 Fig2:**

Example of sampling times for the self-report assessments. The total sampling period covers 28 days

Participants will be asked to complete their reports preferably immediately after they receive a text message with the link to the questionnaires. To minimize memory distortion, the link expires after 30 min. Participants will be sent a reminder text message after 15 min if they did not complete the measurement yet. During the ESM period, the registration of the questionnaires is regularly checked in RoQua. In case of > 10 subsequent missing measurements, participants will receive a telephone call to ask whether they want to stop the ESM measurements. Technical support will be available throughout the study.

For both ESM modules, each measurement starts with questions about the participants’ current mood (PA, NA) and physical state, followed by questions regarding activities for the Do-module and hassles/uplifts and positive/negative thoughts for the Think-module. In addition, the morning measurements include a question about sleep, and the evening measurements a few general questions on how participants experienced the past day and how they feel about the next day. The self-assessments will be rated on dichotomous scales (e.g., for the presence of hassles/uplifts) and visual analogue scales (usually ranging from not at all (0) to very much (100)). The items for the momentary questionnaires are presented in Additional file 1: Table S1.

Participants in the intervention groups receive personalized feedback after each intervention week based on the ESM measurements. This sums up to a total of 4 feedback moments. After weeks 1–3, feedback will be e-mailed to the participant in a digital report comprising text and simple graphs (e.g., pie charts, bar graphs). After week 4, a final feedback report will be e-mailed, in which participants will also receive feedback on temporal relationships between sets of variables (e.g., PA and physical activity (Do-module), or NA and rumination (Think-module)). To this end, time-series analysis will be employed on the individual time series at the end of the ESM period. Specifically, vector autoregression (VAR) models will be applied, which are particularly suited for the investigation of the temporal dynamics between two variables [29, 30].

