For both ESM modules, the feedback reports will contain increasingly rich information across the intervention period by showing participants’ changes in affective responses in daily life situations from week to week. This way, the participants could become more aware of small improvements and get increased control over influences on their mood. In the Do-module, the feedback will also show changes in activities since the start of the study and ultimately provide information on the relationship between affective responses in daily life and activities in order to refocus and redirect the participants towards occasions for emotional strength. In the Think-module, the feedback will not only show participants’ changes in mood, but also negative and positive thinking patterns across the intervention period. The final report of the Think-module will provide information on the relationship between affective responses in daily life and thinking patterns such as rumination in order to make participants aware of potential negative spirals.

A research assistant will discuss the final feedback report with the participant during a debriefing session, which takes place at the mental health care organization shortly after the end of the intervention period. The research assistant will answer questions and help participants provide meaning to the graphs according to a standardized protocol. Personal notes will be made on the printed feedback report, which the participant will take home. Feedback reports are not sent to the (future) therapist by the researcher; participants can choose for themselves whether or not they want to share this information. After discussing the feedback report, participants fill out an evaluation questionnaire on the ESM intervention and the regular questionnaires (control participants fill out the latter at home). At a later point, the intervention tool will also be evaluated through an additional semi-structured interview in a subset of participants. Participants are provided with an information letter about this interview at the end of the debriefing session.

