#### Other study parameters

To investigate whether ESM-derived feedback may be a cost-effective strategy in participants with depression from a societal perspective, we will administer questionnaires for costs due to illness and illness related costs (TiC-P: Trimbos/iMTA questionnaire for Costs associated with Psychiatric Illness [36], adjusted for a mental health population), and quality of life (Euroqol-5D) [37]. Similar questionnaires have also been used in the previous RCT [15] to perform cost-effectiveness and cost-utility analyses [17, 38]. In addition, we will extract information on care use in the 2-year period after participation in ZELF-i from the patient registries of the involved mental health care organizations and from the regional psychiatric case registry (https://www.rgoc.nl/#home/onderzoek/Register), which will be linked to our sample when approved by the participant (as stated on the informed consent form).

To assess patient-experienced utility of the ESM modules, we will administer an evaluation questionnaire after the ESM period. A small, randomly selected number of participants (see sample size calculation) will be invited to partake in a semi-structured interview with an experienced practitioner. Central topics in this semi-structured interview will include personal experiences with the intervention in relation to depressive complaints (burden, motivation), daily functioning, impact on daily rhythm, self-management, and self-insight. In addition, participants will be asked what improvements can be made in the ESM modules and how the intervention could be implemented in standard care. The interviews will generate qualitative data.

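### Adverse events are collected passively while the ESM arms have more planned staff contact than controls, so adverse-event counts would not be comparable between arms

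*Protocol article*

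**What the plan says.** The rule for adverse events stands in the Data management section. It covers "Any undesirable experience reported spontaneously by the participants or observed by the investigator or her staff during the study", and such an experience, "whether or not considered related to the experimental treatment, will be recorded as an adverse event". No question put to all participants is described. The same section says that no data monitoring committee was set up, because the risk added to usual care is judged negligible.

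Contact with study staff is set out under Procedure:

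- **All arms, baseline.** "The introduction session will take place at the mental health care organization", and allocation and the baseline questionnaires happen there.
- **ESM arms, during sampling.** After more than 10 missed measurements, "participants will receive a telephone call to ask whether they want to stop the ESM measurements".
- **ESM arms, end of the 28 days.** A research assistant goes through the final report face to face, and the participant then fills in the questionnaires. For this same assessment, "control participants fill out the latter at home".
- **ESM arms, a subset.** Randomly selected participants are telephoned within 8 weeks of the debriefing and invited to a one-hour interview.
- **All arms, 1, 2, 3 and 6 months.** Invitations come by e-mail, with e-mail and text reminders after 3 days. "The participants will be able to fill out these forms at home".

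The abstract describes the comparator as "a control group receiving no additional intervention".

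**The concern.** A passive rule finds an event only if the participant volunteers it or a staff member notices it. Both become more likely with each conversation, and here the number of planned conversations depends on the allocated arm. Because events are recorded whatever their cause, the control arm is the only guide to how many events would have occurred anyway in a depressed outpatient population. It is also the arm that staff observe least.

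This matters because the protocol itself names a way in which the intervention might harm. Under Other study parameters it says that attending more closely to mood could set off negative thinking in cognitively reactive participants, and one module is built around negative affect and thinking patterns. If adverse events were later reported by arm, an excess under ESM could be harm, contact or both, and equal counts could hide a real difference. In the Discussion section the extra appointment is acknowledged, but only as a possible beneficial attention effect on outcome. Its effect on the detection of harm is not considered.

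**Working it through.** The documents give no adverse-event rate, detection probability or harm test, so there is no figure to reproduce. The check sets planned contacts side by side, using the planned 50 participants per arm (2 x 50 = 100 ESM, 50 control) and the Procedure subsections.

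| Planned contact after the introduction session | ESM arms (100) | Control (50) |
|---|---|---|
| Telephone call during the 28 days | Only after more than 10 missed measurements | None |
| Face-to-face debriefing | All 100, if none drop out | None |
| Interview | About 8-10 per module, so 16-20 in total | None |
| E-mail or text for questionnaires, 1-6 months | Yes | Yes |

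Only the last row is the same in all arms. The first three are the occasions on which staff could observe or be told something in conversation.

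**How unequal detection passes into the counts (assumed values only).** Let observed risk = true risk x detection probability. Then

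observed RR = (true risk ESM / true risk control) x (detection ESM / detection control).

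*Equal true risk of 20% in every arm:*

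- detection 0.6 and 0.4: 12% against 8%, RR = 0.12/0.08 = 1.5
- detection 0.8 and 0.4: 16% against 8%, RR = 0.16/0.08 = 2.0
- detection 0.8 and 0.2: 16% against 4%, RR = 0.16/0.04 = 4.0

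A true risk of 10% gives the same ratios, because true risk cancels.

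*Unequal true risk, detection 0.8 and 0.4:*

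- true 20% ESM, 10% control (RR 2.0): 16% against 4%, observed RR 4.0
- true 10% ESM, 20% control (RR 0.5): 8% against 8%, observed RR 1.0

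The last two lines show that real differences still enter the counts, but distorted. In the final case a true halving of risk disappears.

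*Equal detection, for example 0.5 in every arm:* a true RR of 1.0 is observed as 1.0, and a true RR of 2.0 as 2.0.

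The detection probabilities cannot be estimated from the documents, so the ratios of 1.5 to 4.0 return what was assumed. They show the mechanism and are not an estimate of the bias.

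**The case against.** The strongest reply is that the rule governs recording and notification and is not an analysis. The Statistical analyses section plans no between-arm comparison of adverse events. That is correct, and it limits the point to how recorded events could be read.

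A second reply is that the likeliest harm, worsening depression or functioning, is already measured on one schedule in all arms by the IDS-SR and OQ-45 and modelled as time by group. This also stands. A reader might infer that harm after day 28 would go unseen in every arm, or that no harm comparison is possible. The documents do not support either inference: questionnaires are scheduled at 1, 2, 3 and 6 months, and registry care use does not depend on contact with study staff. Symptom scores do not replace event capture, however. The IDS-SR looks back only 7 days, and neither scale is designated for safety.

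Third, controls can report spontaneously, they receive messages, and each centre must pass on events. The telephone call is conditional and the interview reaches few. So it would go too far to say that control events are almost never found, or that a difference reflects contact instead of harm. It would reflect both.

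Fourth, the monitoring-committee decision is a judgement made in advance and does not rest on event counts. This is fair. What remains is that the counts, as collected, could not later confirm it.

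Finally, this is a condensed article, and a fuller protocol may describe active questioning. The point concerns the rule that the article states, and if all arms are in fact asked the same question, the article should say so.

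**Conclusion.** The point holds in limited form. Followed as written, the adverse-event rule gives unequal ascertainment by arm: one universal face-to-face contact, a conditional telephone call and a subset interview in the ESM arms, against no planned face-to-face or telephone contact for controls after baseline. Counts by arm would be confounded by contact and could not support a claim of negligible added risk over usual care.

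The probable direction is inflation of ESM-arm counts, on the assumption that more contact means more events come to light. The size is unknown. The efficacy analyses are unaffected. This is a weakness in harm reporting that should be corrected and is cheap to correct.

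**What to change.** 1. Add one short adverse-experience question, identical in all three arms, to the post-intervention and the 1-, 2-, 3- and 6-month questionnaires. Ask what happened and when, and whether there was a hospital admission or crisis contact.
2. Make the answers the source for any harm reporting by arm.
3. Keep spontaneous and observed events in a separate listing, marked as not comparable between arms.
4. At the post-intervention assessment, have ESM participants answer the item by self-report before the debriefing begins. Otherwise they would answer after a conversation with staff that controls do not have.
5. As an optional supplement, tabulate crisis contacts and psychiatric admissions by arm from the registry data, for which the protocol already says "we will extract information on care use in the 2-year period after participation in ZELF-i from the patient registries". This covers only participants who approved linkage and the time after participation, so it may not reach the intervention month.

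The cost is slightly longer forms and more events to log. Participants know their allocation and may skip questionnaires, so the item reduces detection bias without removing every source of reporting difference.

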### Study parameters

The main endpoints are based on questionnaires, for which a complete overview is presented in Additional file 2: Table S2.

#### Main study parameter

The primary outcome measure to determine efficacy of the intervention will be the change in depression symptom severity as measured by the self-report Inventory of Depressive Symptomatology (IDS-SR, [31]) across 6 time points: baseline, after 4 weeks of ESM and at 4 follow-up measurements at 1, 2, 3, and 6 months (post-ESM). Participants will be followed prospectively to compare the efficacy of the intervention modules mutually and to the control group.

The 30-item self-report **Inventory of Depressive Symptomatology (IDS-SR)** includes all DSM-IV [2] diagnostic criterion items for major depressive disorder, as well as commonly associated symptoms such as irritability [31]. Each symptom item is scored on a scale from 0 to 3, with higher scores denoting greater symptom severity. The time frame for assessing symptom severity is the 7 day period prior to assessment (independent of whether symptoms have been long-standing, chronic, or recent). The IDS-SR is scored by summing the item responses. Either appetite increase or decrease, and either weight increase or decrease are used to calculate the score. If increase and decrease items are both completed, the highest of the two scores is used. The IDS-SR has good psychometric properties with high concurrent and internal validity (Cronbach’s α = .92) and is sensitive to treatment change [31, 32].

#### Secondary study parameters

From a patient perspective, functional outcomes are at least as relevant as clinical outcomes. Therefore, we will also assess change in psychosocial functioning by means of the Outcome Questionnaire (OQ-45) [33]. In addition, we will assess the extent to which individuals regain self-esteem and take control over their own lives by means of the Dutch Empowerment questionnaire (NEL) [34].

The **Outcome Questionnaire-45 (OQ-45)** is a 45-item self-report scale that measures subjective discomfort, disturbance in interpersonal relations, and functioning in social roles such as work and school [33]. Each item is scored on a 5-point scale from never (0) to almost always (4), yielding a range of possible scores of 0 to 180 with higher values indicating the endorsement of pathology. The OQ-45 can be used on a weekly basis and extensive validation in the United States has provided cut-off scores for reliable change and recovery as markers for gauging treatment success. Internal consistency (.90), test re-test reliability (.84 over 3 weeks in untreated participants), and concurrent validity with other scales are high [35]. The OQ-45 can be used regardless of the type of disorder or type of therapy. The Dutch version of the OQ-45 showed similar psychometric properties as the original instrument.

The **Dutch Empowerment questionnaire (NEL)** is a 40-item self-rating scale to assess patient empowerment, developed by the Dutch Trimbos Institute in collaboration with patients [34]. It incorporates six dimensions: professional help, social support, own wisdom, sense of belonging, self-management, and community inclusion. Items are formulated in positive statements of strengths as perceived by the individual and are rated on 5-point scales ranging from 1 (‘strongly disagree’) to 5 (‘strongly agree’), with the 4 items regarding professional health care having the additional option ‘not applicable’. The total score ranges from 40 to 200, with higher scores indicating more empowerment. Previous research has shown construct validity is satisfactory and internal consistency (α = 0.93) is high [34]. The latter has been corroborated by the ESM RCT in depression [17].

#### Other study parameters

To investigate whether ESM-derived feedback may be a cost-effective strategy in participants with depression from a societal perspective, we will administer questionnaires for costs due to illness and illness related costs (TiC-P: Trimbos/iMTA questionnaire for Costs associated with Psychiatric Illness [36], adjusted for a mental health population), and quality of life (Euroqol-5D) [37]. Similar questionnaires have also been used in the previous RCT [15] to perform cost-effectiveness and cost-utility analyses [17, 38]. In addition, we will extract information on care use in the 2-year period after participation in ZELF-i from the patient registries of the involved mental health care organizations and from the regional psychiatric case registry (https://www.rgoc.nl/#home/onderzoek/Register), which will be linked to our sample when approved by the participant (as stated on the informed consent form).

To assess patient-experienced utility of the ESM modules, we will administer an evaluation questionnaire after the ESM period. A small, randomly selected number of participants (see sample size calculation) will be invited to partake in a semi-structured interview with an experienced practitioner. Central topics in this semi-structured interview will include personal experiences with the intervention in relation to depressive complaints (burden, motivation), daily functioning, impact on daily rhythm, self-management, and self-insight. In addition, participants will be asked what improvements can be made in the ESM modules and how the intervention could be implemented in standard care. The interviews will generate qualitative data.

At baseline, sociodemographic characteristics (gender, age, educational level, work- and living situation), medication use, and current psychotherapy will be assessed by means of a questionnaire. Two additional questionnaires that will be administered are the Twenty-Item Toronto Alexithymia Scale (TAS-20) [39, 40] and the revised version of the Leiden Index of Depression Sensitivity (LEIDS-R) [41, 42]. Alexithymia (literally: “no words for emotions”) is a personality construct that is characterized by difficulties in identifying and describing emotions. Alexithymia is prevalent in approximately 10% of the general population, and 32%–51% of participants with depressive disorders [43, 44]. Since our intervention requires participants to repeatedly rate themselves on various emotional states, participants with high alexithymia scores may find it more difficult to benefit from the intervention. The LEIDS-R will be administered to assess cognitive reactivity, that is the degree to which negative thinking patterns are triggered by depressed mood. The intervention requires participants to focus on their mood states, and will possibly be less beneficial for participants who are highly cognitively reactive, because an increased focus on their mood may trigger negative thinking patterns.

